### Outcome adjudication

An outcome adjudication committee will adjudicate SAEs and AESI on a regular interval. This committee will consist of two experienced vascular neurologists. The committee will receive outcome information blinded to treatment allocation.

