## Methods

### Trial design

ACTION (www.action-study.nl) is an investigator-initiated, phase II, prospective, randomised trial with open label treatment and blinded end-point assessment (PROBE). There will be three arms (1:1:1). In the first arm, participants will receive a high-dose of intravenous anakinra in addition to standard medical management, in the second arm, a subcutaneous low-dose of anakinra in addition to standard medical management, and the third arm constitutes of standard medical management without anakinra. Patients in all arms will get standard medical management. Each treatment arm will include 25 patients. The primary aim of the trial is to study whether use of anakinra has an effect of PHO compared to standard medical management; for this analysis we will combine the two anakinra treatment arms. In the secondary analysis we will investigate whether a difference in dosage of anakinra modifies the effect of anakinra on PHO. Main reasons for studying whether such a difference exists, is that the subcutaneous administration of anakinra is easier in use and has lower costs than the intravenous administration, which on the other hand might be more effective.

The study will be conducted according to the principles of the Declaration of Helsinki and in accordance with the Medical Research Involving Human Subjects Act (WMO). The study was approved by the medical ethics committee of the region Arnhem-Nijmegen (reference NL76607.091.21).

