### Randomisation

Participants will be randomised in the ratio of 1:1:1 via a secure web-based internet system (CastorEDC). Treatment allocation will be stratified for centre of participation, admission ICH volume (10–30 mL vs >30 mL as estimated with the ABC/2 method on non-contrast CT at admission) and renal function (estimated glomerular filtration rate (eGFR) 30–49 vs >50 mL/min/1.73 m^2^) to ensure balance in factors associated with development of PHO and anakinra plasma concentrations. Treatment allocation is not blinded to participants nor to study team members, compatible with the open-label treatment in the PROBE design. Instead, outcome assessment will be blinded for treatment allocation.

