### Adverse event reporting

Adverse events (AEs) are defined as any undesirable experience occurring to a subject during the study, whether or not considered related to the administration of anakinra or other study procedures. Serious adverse events (SAEs) are AEs that result in death, are life-threatening, require hospitalisation or prolongation of existing hospitalisation, result in persistent or significant disability, are congenital anomalies or birth defects, or other important medical events, based on the judgement by the study team. All (S)AEs reported spontaneously by the subject or observed by the investigator will be recorded. Despite the excellent safety record of anakinra and the relatively high number of complications of the disease under study, we will identify the following ‘adverse events of special interest’ (AESIs) to assess participants’ tolerability to anakinra:

*Early neurological deterioration*, defined as *a* ⩾ 2 point decrease in GCS or a ⩾4 point increase in the NIHSS score sustained for at least 8 h, within the first 3 days of hospitalisation;*Infection*, categorised as urinary tract infection, pneumonia, bloodstream infection, or other infections. Infections will be diagnosed and categorised based on the Centers of Disease Control and Prevention (CDC) definitions^
29
^;*Skin injection reaction*, defined as one or more of the following: erythema, ecchymosis, inflammation, and severe pain;*Allergic reaction*, defined as an untoward reaction to anakinra developing over minutes to days after treatment initiation, and is clinically characterised by skin-mucosal, respiratory and/or cardiovascular symptoms. This does not include known side effects of anakinra;*Anaphylaxis*, which is considered when two or more of the following occur during an allergic reaction: generalised involvement of the skin-mucosal tissue, respiratory compromise, reduced blood pressure or associated symptoms, or persistent gastrointestinal symptoms;*Neutropenia*, defined as an absolute neutrophil count (ANC) <1.5 × 10^9^/L.

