### Data and safety monitory board

Study safety will be monitored by an independent data and safety monitory board (DSMB) consisting of a neurosurgeon, a neurologist, and a biostatistician. Interim analyses will be performed after completion of the follow-up period of 24 and 48 participants and will assess the adjudicated events to evaluate safety of the intervention, compared to standard care. The stopping rule for premature ending of the trial because of safety reasons is at least two times (i.e. ⩾200%) higher proportion of participants with an urgent medical reason for withdrawal in the two intervention arms combined and compared to the comparator arm (2:1), with at least two events per group. Results of the interim analyses can be compared between the high dose and low dose treatment arms, to advise on termination of a single treatment arm in case ⩾75% of the withdrawals should occur in one treatment arm.

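### Allergic reaction and anaphylaxis are defined by anakinra exposure, so they cannot be adjudicated blind to anakinra versus control and cannot occur in the control arm

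*Protocol article*

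**What the plan says.** Under Outcome adjudication, the protocol article says "An outcome adjudication committee will adjudicate SAEs and AESI on a regular interval", and then "The committee will receive outcome information blinded to treatment allocation". No event type is exempted.

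Under Adverse event reporting, six AESIs are listed. Allergic reaction is "defined as an untoward reaction to anakinra developing over minutes to days after treatment initiation", with the qualification "This does not include known side effects of anakinra". Anaphylaxis requires at least two listed features during an allergic reaction. Skin injection reaction is "defined as one or more of the following: erythema, ecchymosis, inflammation, and severe pain". Early neurological deterioration, infection and neutropenia have definitions that do not mention the study drug. The same section lists four urgent reasons for withdrawal, one of which is anaphylaxis following anakinra.

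On design, "Treatment allocation is not blinded to participants nor to study team members, compatible with the open-label treatment in the PROBE design" (Randomisation), and "the third arm constitutes of standard medical management without anakinra" (Trial design). No placebo is described.

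The adjudicated events are used twice. At the interim looks the safety board "will assess the adjudicated events to evaluate safety of the intervention, compared to standard care" (Data and safety monitory board). At the end, AESIs and urgent withdrawals are compared between the three arms in 2 × 3 tables with Fisher's exact test (Statistical methods).

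**The concern.** A blinded adjudicator has to be able to apply the event definition without the allocation. For allergic reaction and anaphylaxis the allocation is part of the definition. If the drug is removed from the file, the criterion cannot be judged; if it is left in, the blind is lost. The unqualified blinding statement and these two definitions therefore cannot both hold.

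The same wording affects the analysis. An event defined as a reaction to anakinra cannot be counted in a patient who never received it, so a three-arm test of such an event does not compare risks. A control patient with a clinically identical reaction to another agent would not be counted.

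Because treatment is open label, blinded adjudication is the article's stated safeguard for these safety events. If the wording stays, the trial report would describe two event types as blindly adjudicated when they could not have been, and would offer a between-arm test whose control cell is fixed at zero.

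**Working it through.** The plan gives no figure to reproduce here. The check is mainly a reading of the six definitions side by side.

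**Step 1. Classify each AESI by its own definition (Adverse event reporting).**

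| AESI | Does the definition depend on anakinra? | Can a control patient meet it? |
|---|---|---|
| Early neurological deterioration | No: GCS or NIHSS change of stated size and duration | Yes |
| Infection | No: CDC definitions | Yes |
| Skin injection reaction | No: four local signs; only the label implies an injection | Not excluded by the definition |
| Allergic reaction | Yes: names anakinra and excludes its known side effects | No |
| Anaphylaxis | Yes: through allergic reaction | No |
| Neutropenia | No: laboratory threshold | Yes |

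Count: 2 of 6 depend on anakinra, 1 of 6 is suggestive through its label, and 3 of 6 are neutral. The SAE definition is also neutral.

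**Step 2. What a confirmed event reveals.** The control arm receives no anakinra, so a confirmed allergic reaction or anaphylaxis means that the patient was in one of the two anakinra arms. Both arms receive the drug, so the dose arm is not revealed.

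**Step 3. What the three-arm test does with such an event.** Take 25 patients per arm and let a, b and c be the numbers of patients with the event (high dose, low dose, control), with t = a + b + c. The probability of a table is

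P(a, b, c) = C(25,a) · C(25,b) · C(25,c) / C(75,t),

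and the Fisher p-value sums P over all tables no more probable than the one observed. By definition c = 0.

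- Four events, all in one anakinra arm: C(25,4) / C(75,4) = 12,650 / 1,215,450 = 0.0104. The three tables with all four events in a single arm are the least probable, so p = 3 × 0.0104 = 0.031.
- Four events in each anakinra arm, none in control: p = 0.115.
- Five events in each anakinra arm, none in control: p = 0.040.

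The document gives no rate for these reactions. These counts are illustrations of how the test behaves, not predictions.

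**Step 4. Link to the withdrawal rule.** Of the four urgent withdrawal reasons, three can arise in any arm (neutropenia, surgical evacuation of the haematoma, moribund deterioration). The fourth, anaphylaxis after anakinra, can arise only in the anakinra arms. It enters both the interim rule, which compares the combined anakinra arms with control, and the final Fisher comparison of withdrawals.

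**The case against.** The best defence is that this is an article. Redaction, packet content and order of review belong in an adjudication charter that is not shown, and their absence here is no finding. That is right as far as it goes, but redaction cannot repair a criterion that itself contains the exposure.

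A second defence is that the clinical part of the allergic reaction definition (skin-mucosal, respiratory or cardiovascular symptoms) is neutral. It could be judged blind, with exposure linked afterwards. This is workable, but it amounts to adjudicating a drug-neutral definition, which the article does not state.

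A third is that the practical reach is small. Only one of four urgent withdrawal reasons is involved. The other AESIs have numerical thresholds or CDC definitions that limit discretion. This stands and keeps the point modest.

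A reader might infer more than the text supports:

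- **Three of six AESIs unblind.** The skin injection reaction definition does not name the drug. The low-dose arm is the only one with scheduled subcutaneous study injections, so the label is suggestive. However, high-dose patients are treated intravenously and controls might receive routine injections (an assumption). It is not conclusive.
- **The dose arm is disclosed.** The two drug-conditional definitions separate anakinra from control only.
- **Unblinding carries over to infection and neurological deterioration in the same patients.** This needs adjudicators to see one patient's events together, with the revealing event before or alongside the others. The article says nothing about linkage or order. Carry-over is possible but not shown, and no number of affected patients can be given.

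**Conclusion.** The point holds for two of the six AESIs and, through anaphylaxis, for one of the four urgent withdrawal reasons. For these, the statement of blinded adjudication is incompatible with the definitions, and the control count in the three-arm comparison is zero by construction.

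It does not follow that the blind fails for the safety comparison as a whole. Early neurological deterioration, infection, neutropenia and other SAEs can still be adjudicated blind. The primary outcome is read from MRI by assessors blinded to allocation and is unaffected.

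The conclusion rests on the published wording and on a control arm without anakinra. It needs no assumption about event rates or about how files are assembled. No bias in any result is demonstrated. The change is still worth making, because it determines what can be claimed about two drug-relevant safety events.

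**What to change.** Preferred: for adjudication, define allergic reaction and anaphylaxis without reference to the study drug (a reaction to any suspected agent, with the existing clinical features and a time window that applies in every arm). They can then be judged blind and counted in all three arms. Attribution to anakinra can be recorded separately after adjudication.

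Alternative: keep the drug-specific definitions, restrict the blinded-adjudication statement to the arm-neutral events, and report these two descriptively as unblinded, drug-specific events outside the three-arm Fisher test. This option must also say how an anaphylaxis that meets the SAE definition is handled; otherwise it returns to the blinded committee as an SAE.

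Under either option, the urgent withdrawal reason that names anakinra (Adverse event reporting) and the interim safety rule that uses it (Data and safety monitory board) must be reconciled with the wording adopted.

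The cost is a wording change, with no new procedures or patients. The downside is small. A neutral definition may count a few reactions to other agents; under the alternative, these two events lack blinded central adjudication.

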### Data and safety monitory board

Study safety will be monitored by an independent data and safety monitory board (DSMB) consisting of a neurosurgeon, a neurologist, and a biostatistician. Interim analyses will be performed after completion of the follow-up period of 24 and 48 participants and will assess the adjudicated events to evaluate safety of the intervention, compared to standard care. The stopping rule for premature ending of the trial because of safety reasons is at least two times (i.e. ⩾200%) higher proportion of participants with an urgent medical reason for withdrawal in the two intervention arms combined and compared to the comparator arm (2:1), with at least two events per group. Results of the interim analyses can be compared between the high dose and low dose treatment arms, to advise on termination of a single treatment arm in case ⩾75% of the withdrawals should occur in one treatment arm.

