All SAEs and AESI reported spontaneously by the subject or observed by the investigator will be recorded from baseline to day 90. Specific urgent medical reasons to withdraw from the trial have been defined and will be monitored closely: neutropenia, neurosurgical haematoma evacuation, anaphylaxis after anakinra administration, and severe clinical deterioration in which the condition of the participant is considered to be moribund and active treatment is discontinued.

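### The trial-level safety stopping rule needs at least two control-arm events, so with none or one in controls it cannot be met, whatever happens on anakinra

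*Protocol article*

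**What the plan says.** The section on the data and safety monitoring board sets the looks: "Interim analyses will be performed after completion of the follow-up period of 24 and 48 participants". Allocation is equal across three arms (Randomisation: "Participants will be randomised in the ratio of 1:1:1"), so about 8 controls and 16 anakinra participants are expected at the first look, and 16 and 32 at the second.

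The trial stops for safety if there is an "at least two times (i.e. ⩾200%) higher proportion of participants with an urgent medical reason for withdrawal". The sentence then fixes the groups and the minimum count: the excess is judged "in the two intervention arms combined and compared to the comparator arm (2:1), with at least two events per group".

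The events that count are listed under Adverse event reporting: "neutropenia, neurosurgical haematoma evacuation, anaphylaxis after anakinra administration, and severe clinical deterioration", the last of these in a moribund participant whose active treatment is discontinued.

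A second provision follows in the same section. The two dose arms can be compared with each other, "to advise on termination of a single treatment arm in case ⩾75% of the withdrawals should occur in one treatment arm".

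The article gives no expected rate for these events and no error rate or power for the rule.

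**The concern.** The two groups in the stopping sentence are the combined anakinra arms and the comparator arm. A minimum of two events in each therefore makes the rule conditional on controls having events. That runs against its purpose: the safer standard care turns out to be, the less able the rule is to register an excess on anakinra. One counted reason, anaphylaxis following anakinra, cannot occur in a control participant at all, so it can never help to satisfy the control minimum.

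The treatment is open-label and one arm receives a high intravenous dose. A boundary fixed in advance should respond to a clear imbalance. This one cannot respond to the starkest imbalances, and its behaviour at these sample sizes is not reported.

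A smaller wording point concerns the threshold. Two times is a ratio of 2, whereas 200% higher, taken literally, is a ratio of 3.

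**Working it through.** **Inputs.** Looks at 24 and 48 participants, 1:1:1 allocation, and the two-event minimum come from the protocol. Exact splits of 8 v 16 and 16 v 32 (control v anakinra) are assumed. Event rates are assumed over a range. The plan states no operating figure for the rule, so there is none to reproduce.

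**Rule as coded.** With Xc events among nc controls and Xa among na on anakinra, the rule fires if Xc ≥ 2, Xa ≥ 2 and Xa/na ≥ k × Xc/nc. Here k = 2 is the 2-fold reading and k = 3 the 3-fold reading.

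**Step 1: what can fire, with no assumption on rates.** If Xc is 0 or 1, the first condition fails and Xa is irrelevant. So 16/16 v 1/8 (Fisher exact p = 0.00002) does not meet the rule, nor does 32/32 v 1/16. Since na/nc = 2, the third condition is Xa ≥ 2k × Xc. At Xc = 2 the smallest firing results are:
- 2-fold: Xa = 8, that is 8/16 v 2/8 or 8/32 v 2/16;
- 3-fold: Xa = 12, that is 12/16 v 2/8 or 12/32 v 2/16.

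**Step 2: how often control has fewer than two events.** P(Xc < 2) = (1 − p)^n + n p (1 − p)^(n−1). For p = 0.05 and n = 8: 0.95^8 + 8 × 0.05 × 0.95^7 = 0.663 + 0.279 = 0.94.

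| Control rate | Look 1 (n = 8) | Look 2 (n = 16) |
|---|---|---|
| 5% | 0.94 | 0.81 |
| 10% | 0.81 | 0.51 |
| 20% | 0.50 | 0.14 |
| 25% | 0.37 | 0.06 |

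**Step 3: chance of firing at either look.** Exact enumeration of independent binomial counts, with second-look counts cumulative, on the 2-fold reading:

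| Control v anakinra | Fires at either look |
|---|---|
| 0% v any rate | 0 |
| 5% v 30% | 0.12 |
| 10% v 30% | 0.25 |
| 20% v 40% | 0.44 |
| 20% v 50% | 0.62 |

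On the 3-fold reading, 10% v 30% falls from 0.25 to 0.06, and 20% v 40% from 0.44 to 0.16.

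**Step 4: what the control minimum buys.** False alarms at either look with equal rates in all arms, 2-fold reading, keeping the minimum of two anakinra events:

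| Common rate | As written | Control minimum deleted |
|---|---|---|
| 5% | about 0% | 27% |
| 10% | 0.3% | 37% |
| 20% | 7% | 34% |

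The minimum does limit false alarms, so deleting it and changing nothing else is not a sufficient repair.

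**The case against.** Four points can be made for the plan.

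**The rule is not the only safeguard.** A reader might infer that this is the sole safety boundary, or that harm on anakinra would pass unnoticed. The documents do not support that. The single-arm provision has no control minimum: 6 high-dose, 1 low-dose and 1 control event would meet it, since 6/8 = 75%. The board is independent, includes a biostatistician and reviews adjudicated events, and nothing limits it to the numerical rule. This stands, within limits. The provision is advisory and does not respond when events are split across both doses. At 16/16 v 1/8, each dose arm holds 8 of 17 events (47%), so neither provision is met. Judgement can override a faulty rule but does not correct it.

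**Control events may be common.** The counted reasons include moribund deterioration and haematoma evacuation, and the sample size section allows 25% drop-out because of the severity of the disease. Drop-out is not the same quantity, but control rates of 20% to 25% deserve a place beside 5% and 10%. This also stands. At those rates the control minimum is usually reached by the second look, and the rule is weak rather than inert.

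**The threshold is clear enough.** A reader might infer that the plan sets two conflicting thresholds. The protocol's own gloss equates 200% with two times, which favours the 2-fold reading. The bracketed 2:1 does not settle it, because it may be only the allocation ratio. This is a wording point.

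**The minimum prevents false alarms.** It does, as step 4 shows. That argues for some safeguard, but not for one that depends on the control arm.

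**Conclusion.** The rule is wrong as written. On its plain reading, the trial-level rule cannot be met with 0 or 1 control events. That follows from the sentence itself and needs no assumption about event rates.

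How often this matters does depend on assumption. Under exact 8 v 16 and 16 v 32 splits and independent events, the chance of too few control events at the second look runs from 0.81 at a 5% control rate to 0.06 at 25%. The chance of firing at either look runs from 0.12 (5% v 30%) to 0.62 (20% v 50%).

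The gap is therefore specific: harm spread over both doses with at most one control event. Harm concentrated in one dose arm has the advisory provision, and an excess over two or more background control events can trigger the rule, though often with low probability. The primary efficacy analysis is unaffected. The 2-fold or 3-fold question is secondary.

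**What to change.** Reword the stopping sentence so that the minimum number of events does not depend on the control arm; any minimum can sit on the anakinra arms or on the total. Do not simply delete the control minimum. The sponsor and the monitoring board should agree the accompanying criterion from its computed operating characteristics at both looks, over a range of control rates that includes 20% to 25%, and report them. No particular criterion is proposed here.

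In the same edit, state the threshold once as a ratio of proportions, and say whether the bracketed 2:1 is the threshold or the allocation ratio.

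The cost is a wording amendment to the protocol and, where one exists, the board's charter, with no extra participants or data. The price is a somewhat higher false-alarm rate than the present rule, to be weighed openly against better detection.
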